## Secondary

1. To assess if access to zinc treatment for diarrhea in the home in addition to zinc treatment of diarrhea in the clinic decreases the likelihood of recurrent diarrhea episodes
2. To assess if access to zinc treatment for diarrhea in the home in addition to zinc treatment of diarrhea in the clinic leads to a reduction in the prevalence of acute respiratory infections
3. To assess if access to zinc treatment for diarrhea in the home in addition to zinc treatment of diarrhea in the clinic results in reduction in antimicrobial use
4. To assess whether treatment of diarrhea with zinc in the clinic leads to a decrease in diarrhea prevalence from baseline rates of diarrhea before introduction of zinc
5. To assess difference in zinc utilization practices in parent initiated home treatment vs clinic treatment communities
   1. frequency of use and adherence to treatment instructions
   2. who receives zinc
   3. used for what indications
6. To compare cost estimates and estimate cost benefits
7. To assess acceptability and satisfaction with a home treatment program among providers and caretakers

# Study design

*Study site and population* -- This study will take place the area of Asembo within 4.25 kilometers of Lwak Hospital where CDC’s IEIP program has ongoing population-based surveillance for infectious disease syndromes.

Since September 2001, KEMRI and CDC have collaborated to operate a demographic surveillance system (DSS) in Bondo and Siaya Districts in Western Kenya. Two rural study sites near Lake Victoria, Asembo and Gem, are covered by the DSS, totaling a population of approximately 130,000 people living in approximately 34,000 households. The area is large (almost 400 km2), culturally homogeneous (95% Luo tribe); subsistence farming and fishing constitute the principal economy. The area has perennial, high-level malaria transmission and a high rate of HIV infection (2003, >10% men, >20% women aged 13-34 years). Other infectious diseases are also common in the area. Consequently, the area has mortality figures that reflect this burden of infectious diseases --- infant mortality rate (120 per 1,000 live births) and a life expectancy at birth of 38 years. The area is one of the most impoverished in Kenya; 60-70% of people live below the poverty line in Siaya and >70% in Bondo (Kenyan Central Bureau of Statistics, 1997). The area has high rates of migration -- in 2002, the rate of out-migration was 115 per 1,000 person-years and in-migration was 124 per 1,000 person-years.

The Lwak surveillance area includes 33 villages, with an approximate enrolled population of 23,000 people. Enrollment of villages began in October 2005 and was completed in June 2006. Homes are visited every two weeks by field workers who enquire about symptoms of key infectious diseases, like diarrhea, respiratory infections and malaria. For key symptoms, like diarrhea, cough and fever, the actual number of days of symptoms are recorded. Some basic measurements, such as temperature and respiratory rate, are taken. Health seeking in the last two weeks is also asked about. This is being done for children and adults.

*Inclusion criteria.* All children 2 to 59 months of age in households within selected villages that are already enrolled in the IEIP morbidity surveillance project (KEMRI SSC # 985; CDC IRB # 4678) will be eligible for enrollment. Children born into the study area after the start of the study will also be eligible for enrollment after they reach 2 months of age. Recruitment and enrollment will be done by field workers working for the study, who will read the consent form to guardians of all eligible participants that explains the study.

*Exclusion criteria.* Children under 2 months of age will not be eligible for enrollment, until they reach 2 months of age as the role of zinc has not been well-studied in neonates. Children of parents who do not give written informed consent for their participation will not be enrolled.

*Randomization.* This will be a cluster-randomized study. Thirty-three villages in Asembo participating in the morbidity surveillance (see below) will be selected to participate in this study. The villages will be randomized as 16-17 villages for zinc + ORS at home and clinic villages and 16-17 villages and ORS at clinic only villages. All eligible and participating children within a village will get the same treatment. A form will be filled out to keep track of the enrollment (appendix K). See figure.

Select 33 villages in Asembo closest to Lwak clinic

Obtain community approval

of chiefs and subchiefs

Home Zinc 10 days + low osm ORS

Referral to clinic

15 villages

No home zinc or ORS

Referral to clinic

15 villages

Continue biweekly household

visits for incident and prevalent

diarrhea, ARI, fever illness

Incident diarrhea episodes

Obtain parental consent of

children < 5 years

Baseline survey of prevalence

of diarrhea, ARI, malaria

Randomly assign to home zinc

and no home zinc villages

biweekly household

visits for incident and prevalent

diarrhea, ARI, fever illness

*Baseline survey and measurements.* All enrolled households will have a baseline survey done at the beginning of the study. The survey will collect the following data (Appendix B).

- Diarrhea management and care seeking practices
- Household characteristics
- Socio-demographic characteristics of household
- Water & sanitation exposures/practices
- Knowledge & attitudes about zinc, other micronutrients
- Height & weight
- Insecticide treated bednet use
- ORS awareness/use
- Antimicrobial use

### In addition, 165 children (5 per village selected randomly) will have a baseline serum zinc level measured, following parental informed consent (appendix J). This is to compare the baseline zinc status in the two groups. These same 165 children will also have a hemoglobin tested at the beginning of the study. Hemoglobin will be tested using a Hemocue machine. Children with anemia will be treated according to KMOH guidelines as follows:

### Hb 5-11 gm/dl - iron tablet or syrup and folate tablet for 14 days dosed according to age (Hb < 5 gm/dl – referral to hospital.

*Procedures for household visits.*  Field workers will visit each enrolled child every 2weeks. S/he will ask about episodes of diarrhea since the last visit as well as current episodes. S/he will also record symptoms of acute respiratory illness and malaria, as well as any health seeking and medications resulting from these illnesses (Appendix C). S/he will ask about recent or current fever and any health seeking and medications resulting from the recent or current fever. S/he will also inquire about any use of zinc in the last two weeks. The number of days of zinc and number of pills of zinc will be documented. The interviewer will ask to see the zinc blister pack and record how many pills are remaining.

*Administration of zinc*

In the villages/clusters randomized to no home zinc, parents will be instructed by the field workers to take their children to the clinic if they have diarrhea, defined as an episode having 3 or more loose or watery stools (+/-) blood in a 24 hour period. At the clinic, the child will be evaluated by a clinical officer. If the child meets the above definition of diarrhea, they will be given zinc and ORS as described below.

In the villages/clusters randomized to home zinc, parents will be supplied with one 10-day blister pack of zinc and 3 satchets of ORS for each child in the house under 5 years of age. Zinc packs and ORS satchets will be given once every 2 months, regardless of whether the zinc was used in the previous month. Parents will be given instructions on how to use zinc and ORS at the beginning of the study and every 2 months thereafter when the zinc is given to them by a village reporter (a traditional birth attendant) or a community health worker. Parents in these villages/clusters will also be instructed to take their children to the clinic if they have diarrhea. They will be specifically instructed that taking zinc and ORS should not prevent them from taking their child to the clinic. Particular emphasis will be made that any child with diarrhea, *and* another symptom such as fever or cough, should definitely be taken to the clinic – that zinc is not adequate treatment for a child with fever or cough, who might need an antimalarial or an antibiotic. If the field worker on his biweekly visit finds out that the mother has given zinc to a child not meeting the diarrhea case definition, he will not tell the mother to stop the course of zinc. This is for several reasons. First, the field worker will not be medically trained and so will not be trained to apply the case definition of diarrhea. Second, diarrhea is a symptom taken by history, so that if the mother reports the child has diarrhea, the field worker will not really be able to assess the accuracy of that symptom. Third, there will be no adverse effects from the course of zinc – daily zinc supplementation regardless of illness has been shown to be beneficial in some studies (Zinc Investigators Collaborative Group 1999, Zinc Investigators Collaborative Group 2000). However, the field worker will encourage all mothers of children with diarrhea, especially those with fever, cough or another symptom, to go to the clinic to be seen by a clinical officer. The use of zinc for episodes of diarrhea will be evaluated on a biweekly basis based on the data collected by the field workers to assure that zinc is not being given alone when the child has other symptoms, such as fever and cough. If a significant number of mothers are giving zinc inappropriately without seeking care for other symptoms, further education in the use of zinc in the home will be given. Community health workers or village reporters, different from the field workers who do the biweekly visits, will make home visits every month during the first 3 months of the study to ensure that mothers understand the proper use of zinc and ORS for treatment of diarrhea. After the first three months, the village reporter or community health worker will visit the home every 3 months. On each home visit, the village reporter will ask some questions to assess whether mother is using zinc correctly (appendix L).

At the clinic, the child will be evaluated by a clinical officer. If the child meets the above definition of diarrhea, the clinical officer will inquire if they are already taking zinc for this episode of diarrhea. If they are not already taking zinc and ORS, he will give them zinc and ORS as described below.

Along with instructions regarding how to take zinc, parents will be instructed in the use of ORS and proper fluid management (i.e. encouragement of breastmilk, if breast-feeding, ORS, or food-based fluids, such as soup, enriched uji). Recommended ORS amounts will follow KMOH guidelines. In the first 4 hours, the amount of ORS recommended will be as follows:

| Age | Up to 4 mos | 4-11 mos | 12 mo – 2 yr | 2-5 yrs |
| --- | --- | --- | --- | --- |
| Weight | < 6 kg | 6-<10 kg | 10-<12 kg | 12-19 kg |
| In ml | 200-400 | 400-700 | 700-900 | 900-1400 |

This should be followed by replacement for each loose stool as follows: up to 2 years of age 50-100 ml per stool and 2 years or more 100-200 ml.

Zinc will be administered using the same formulation in the home and in the clinic. Zinc will be administered in the form of a dispersible tablet of zinc-sulfate, 20 mg. A half-tablet, 10 mg, will be administered to children between 2 and 5 months of age. A full 20 mg tablet will be given to children > 6 months of age. The tablet will be dissolved in water, ORS or breast milk and administered to the child. . Mothers will be instructed on using clean water to dissolve tablets for remaining doses. Children who vomit after taking their dose of zinc will not be given another dose that day. The mother will be instructed how to administer the zinc tablet. Zinc will be given once daily for 10 days total. Zinc will be provided in a dispersible zinc tablet and packaged in a 10 tablet blister pack. If the child is holding down fluids and has not vomited in the past 2 hours, then zinc treatment should be started, otherwise the caretaker will be instructed to wait until this occurs.

*Referrals.* If on the day of the field interviewer’s visit, the child has any of the following conditions on the day that the field worker visits the home, the child will be referred to the health clinic

- Diarrhea with
  - moderate to severe dehydration (defined according to IMCI as having 2 or more of the following symptoms: lethargic/unconscious, sunken eyes, not able to drink or breastfeed, skin pinch goes back slowly, restless/irritable) or not able to take ORS
  - Continued illness by the 7th day observation
  - bloody diarrhea
  - persistent diarrhea at any point in the study will be referred to Lwak hospital . Persistent diarrhea is defined as > 14 days of diarrhea.

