### History of fever in the last 24 hours

- Cough and difficult or fast breathing

Care at Lwak clinic for children in the study will be free of charge. Children in the study will be identified at the clinic by an identification card.

*Clinic visits.* All study children will be identified in the clinic by an identification card. They will be seen by a clinical officer hired by the study. Diagnosis and treatment will be according to standard protocols used for childhood illness in peripheral health facilities in Kenya (IMCI. Zinc and low osmolarity ORS will be administered according to MOH protocol. For children in the home zinc group, the clinical officer will inquire if the child is already taking zinc for that episode of diarrhea. If so, then no more zinc will be given. If not, then a 10 day course of zinc will be given. Bloody diarrhea will be treated with nalidixic acid. Uncomplicated malaria will be treated according to KMOH guidelines, artemether/lumefantrine (coartem) as of June 2006. Pneumonia not requiring referral to hospital will be treated with cotrimoxazole or amoxacillin. Children meeting criteria for referral to the hospital according to IMCI guidelines will be hospitalized at Lwak Hospital, and transferred to Bondo District Hospital or Nyanza Provincial Hospital, if appropriate treatment cannot be given at Lwak..

Children with a recent history of or documented fever will have a blood smear for malaria taken. If the results of the blood smear are positive for malaria, the child will be treated for malaria as outlined above. Blood smears will be read by a microscopist at the clinic.

A questionnaire will be filled out for study children who visit the clinic. The questionnaire will ask about symptoms, duration of illness and health-seeking behaviour (Appendix E).

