## Calculation and comparison of incidence rates

Incidence density rates of diarrheal disease will be calculated as number of new episodes of diarrhea per person-time. Using person-time as the denominator can incorporate information from children who are in the study for only part of the time, contributing less than 1 full year of data, due to out-migration, death or birth. 95% confidence intervals will be calculated around point estimates of incidence rates. Incidence rates for acute respiratory illness and malaria will be calculated in the same way as for diarrhea. The mean number of episodes of diarrhea will be compared between the home zinc and nonhome zinc groups using an ANOVA test accounting for repeat episodes of diarrhea within the same child, accounting for potential confounding variables, such as age and season. Potential confounders of the outcome, such as village of residence and age of the child and malaria coinfection, will be controlled for in the final model.

*Calculation and comparison of time to repeat episode of diarrhea.*

The time before a repeat episode of diarrhea in children who have their first episode of diarrhea will be compared between the home zinc and no home zinc groups. The time to a new episode of diarrhea will be measured as the number of days after the last day of the child’s first episode of diarrhea to the first day of the next episode of diarrhea in that child. This analysis will use as a Cox proportional hazards model, in which the child will be censored after the first day of their first repeat episode of diarrhea.

A secondary analysis will compare the number of repeat diarrheal episodes that occur after the first episode of diarrhea. Mean or median number of repeat episodes will be compared by t-test or Wilcoxon rank sum test depending on the distribution of episodes.

*Comparison of the effect of zinc on the treatment of diarrhea.* The mean duration of diarrheal episodes between children in the home zinc and nonhome zinc groups will be compared using ANOVA controlling for potential confounders such as age and season. Repeat episodes of diarrhea in the same children will be accounted for in the analysis. We will also analyze differences in the severity of diarrhea between groups (severe defined as visiting the clinic) and antibiotic use between groups. This will be done using logistic regression with clinic visit and use of antibiotic as the outcome variable.

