| *Noisy breathing* |  |  |  |  |  |  |  |  |  |  |  |  |  |  |  |  |  |  |  |  |  |  |  |  |  |  |  |  |  |  |  |  |
| *Convulsions* |  |  |  |  |  |  |  |  |  |  |  |  |  |  |  |  |  |  |  |  |  |  |  |  |  |  |  |  |  |  |  |  |
| *Unresponsive/*  *lethargic* |  |  |  |  |  |  |  |  |  |  |  |  |  |  |  |  |  |  |  |  |  |  |  |  |  |  |  |  |  |  |  |  |
|  |  |  |  |  |  |  |  |  |  |  |  |  |  |  |  |  |  |  |  |  |  |  |  |  |  |  |  |  |  |  |  |  |
| *Visit Akala* |  |  |  |  |  |  |  |  |  |  |  |  |  |  |  |  |  |  |  |  |  |  |  |  |  |  |  |  |  |  |  |  |
| *Visit other clinic* |  |  |  |  |  |  |  |  |  |  |  |  |  |  |  |  |  |  |  |  |  |  |  |  |  |  |  |  |  |  |  |  |
|  |  |  |  |  |  |  |  |  |  |  |  |  |  |  |  |  |  |  |  |  |  |  |  |  |  |  |  |  |  |  |  |  |
| ***Day of visit*** |  |  |  |  |  |  |  |  |  |  |  |  |  |  |  |  |  |  |  |  |  |  |  |  |  |  |  |  |  |  |  |  |
| *Restless/irritable* |  |  |  |  |  |  |  |  |  |  |  |  |  |  |  |  |  |  |  |  |  |  |  |  |  |  |  |  |  |  |  |  |
| *Lethargic/unresponsive* |  |  |  |  |  |  |  |  |  |  |  |  |  |  |  |  |  |  |  |  |  |  |  |  |  |  |  |  |  |  |  |  |
| *Dehydration?* |  |  |  |  |  |  |  |  |  |  |  |  |  |  |  |  |  |  |  |  |  |  |  |  |  |  |  |  |  |  |  |  |
| *chest indraw?* |  |  |  |  |  |  |  |  |  |  |  |  |  |  |  |  |  |  |  |  |  |  |  |  |  |  |  |  |  |  |  |  |
| *grunting?* |  |  |  |  |  |  |  |  |  |  |  |  |  |  |  |  |  |  |  |  |  |  |  |  |  |  |  |  |  |  |  |  |
| *Temperature* |  |  |  |  |  |  |  |  |  |  |  |  |  |  |  |  |  |  |  |  |  |  |  |  |  |  |  |  |  |  |  |  |
| *Respiratory rate* |  |  |  |  |  |  |  |  |  |  |  |  |  |  |  |  |  |  |  |  |  |  |  |  |  |  |  |  |  |  |  |  |

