**Appendix D. Diarrhea follow-up visit questionnaire (Use one form for follow-up of each diarrheal episode)**

Interviewer code 

Child’s First/Christian Name Juok/middle Name Last/Father’s name

DSS Permanent ID Number. (Use temporary ID if child does not yet have an ID, which should be village, compound, house and “99” for individual ID number. )

**Month:** ____________*(Put 1 in days in which symptom was present, 0 if symptom not present, 9 if don’t know; in row called Followup visit, put 3, 7, or 14 in day of f/u visit)*

| Symptom | 1 | 2 | 3 | 4 | 5 | 6 | 7 | 8 | 9 | 10 | 11 | 12 | 13 | 14 | 15 | 16 | 17 | 18 | 19 | 20 | 21 | 22 | 23 | 24 | 25 | 26 | 27 | 28 | 29 | 30 | 31 |  |
| --- | --- | --- | --- | --- | --- | --- | --- | --- | --- | --- | --- | --- | --- | --- | --- | --- | --- | --- | --- | --- | --- | --- | --- | --- | --- | --- | --- | --- | --- | --- | --- | --- |
| First day diarrhea |  |  |  |  |  |  |  |  |  |  |  |  |  |  |  |  |  |  |  |  |  |  |  |  |  |  |  |  |  |  |  |  |
| Day of first home visit |  |  |  |  |  |  |  |  |  |  |  |  |  |  |  |  |  |  |  |  |  |  |  |  |  |  |  |  |  |  |  |  |
| Follow up visit |  |  |  |  |  |  |  |  |  |  |  |  |  |  |  |  |  |  |  |  |  |  |  |  |  |  |  |  |  |  |  |  |
| Took zinc |  |  |  |  |  |  |  |  |  |  |  |  |  |  |  |  |  |  |  |  |  |  |  |  |  |  |  |  |  |  |  |  |
| Vomit in hour  after zinc |  |  |  |  |  |  |  |  |  |  |  |  |  |  |  |  |  |  |  |  |  |  |  |  |  |  |  |  |  |  |  |  |
| Took ORS |  |  |  |  |  |  |  |  |  |  |  |  |  |  |  |  |  |  |  |  |  |  |  |  |  |  |  |  |  |  |  |  |
| other meds* |  |  |  |  |  |  |  |  |  |  |  |  |  |  |  |  |  |  |  |  |  |  |  |  |  |  |  |  |  |  |  |  |
| Diarrhea |  |  |  |  |  |  |  |  |  |  |  |  |  |  |  |  |  |  |  |  |  |  |  |  |  |  |  |  |  |  |  |  |
| Vomiting/  spit up |  |  |  |  |  |  |  |  |  |  |  |  |  |  |  |  |  |  |  |  |  |  |  |  |  |  |  |  |  |  |  |  |
| Not eat/drink |  |  |  |  |  |  |  |  |  |  |  |  |  |  |  |  |  |  |  |  |  |  |  |  |  |  |  |  |  |  |  |  |
| Fever |  |  |  |  |  |  |  |  |  |  |  |  |  |  |  |  |  |  |  |  |  |  |  |  |  |  |  |  |  |  |  |  |
| Convulsions |  |  |  |  |  |  |  |  |  |  |  |  |  |  |  |  |  |  |  |  |  |  |  |  |  |  |  |  |  |  |  |  |
| Rash |  |  |  |  |  |  |  |  |  |  |  |  |  |  |  |  |  |  |  |  |  |  |  |  |  |  |  |  |  |  |  |  |

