| Irritable/restless |  |  |  |  |  |  |  |  |  |  |  |  |  |  |  |  |  |  |  |  |  |  |  |  |  |  |  |  |  |  |  |  |
| Went to Lwak |  |  |  |  |  |  |  |  |  |  |  |  |  |  |  |  |  |  |  |  |  |  |  |  |  |  |  |  |  |  |  |  |
| Went to other clinic/hospital |  |  |  |  |  |  |  |  |  |  |  |  |  |  |  |  |  |  |  |  |  |  |  |  |  |  |  |  |  |  |  |  |
|  |  |  |  |  |  |  |  |  |  |  |  |  |  |  |  |  |  |  |  |  |  |  |  |  |  |  |  |  |  |  |  |  |
| *Day of visit* |  |  |  |  |  |  |  |  |  |  |  |  |  |  |  |  |  |  |  |  |  |  |  |  |  |  |  |  |  |  |  |  |
| Lethargic/  Unresponsive |  |  |  |  |  |  |  |  |  |  |  |  |  |  |  |  |  |  |  |  |  |  |  |  |  |  |  |  |  |  |  |  |
| Unable to drink |  |  |  |  |  |  |  |  |  |  |  |  |  |  |  |  |  |  |  |  |  |  |  |  |  |  |  |  |  |  |  |  |
| Sunken eyes |  |  |  |  |  |  |  |  |  |  |  |  |  |  |  |  |  |  |  |  |  |  |  |  |  |  |  |  |  |  |  |  |
| Restless/irritable |  |  |  |  |  |  |  |  |  |  |  |  |  |  |  |  |  |  |  |  |  |  |  |  |  |  |  |  |  |  |  |  |
| Skin pinch slow |  |  |  |  |  |  |  |  |  |  |  |  |  |  |  |  |  |  |  |  |  |  |  |  |  |  |  |  |  |  |  |  |
| Temperature |  |  |  |  |  |  |  |  |  |  |  |  |  |  |  |  |  |  |  |  |  |  |  |  |  |  |  |  |  |  |  |  |
| Refer to clinic? |  |  |  |  |  |  |  |  |  |  |  |  |  |  |  |  |  |  |  |  |  |  |  |  |  |  |  |  |  |  |  |  |

*Name(s) of other meds taken for diarrhea. *(observe in home if possible)*  Panadol  Cotrimoxazole  Nalidixic acid  Other ______

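### The two-weekly household form has no medicine row and names Akala instead of Lwak, so follow-up captures antimicrobials for illness without diarrhoea only at Lwak visits

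*Protocol*

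**What the plan says.** Under Study design, Procedures for household visits, the field worker is to record symptoms of acute respiratory illness and malaria together with "any health seeking and medications resulting from these illnesses (Appendix C"). The next sentence adds, for fever, "any health seeking and medications resulting from the recent or current fever", and names no other form for it.

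Secondary objective 3 asks whether home access to zinc "results in reduction in antimicrobial use". It carries no restriction to diarrhoeal illness.

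The one antibiotic analysis described is in Data Analysis, under the comparison of the effect of zinc on the treatment of diarrhea: "This will be done using logistic regression with clinic visit and use of antibiotic as the outcome variable".

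The study clinic is Lwak. The Referrals text says: "Care at Lwak clinic for children in the study will be free of charge".

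**The concern.** The text promises a two-weekly record of medicines and care seeking that the form assigned to it cannot hold. If Appendix C is used as printed, an antibiotic bought or given outside Lwak for cough or fever without diarrhoea leaves no trace during follow-up, and no later analysis can recover it. A Lwak visit reported at the household visit can only be entered under "Visit other clinic", together with every other facility.

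At stake is the part of objective 3 that concerns illness without diarrhoea. Such illness is in scope, since respiratory infection is itself a secondary objective. For it, recorded antimicrobial use would depend on whether the child came to Lwak, and so would not measure use in the community.

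**Working it through.** **Form-by-form check for a medicine field**

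| Form | When completed | Medicine field | Care-seeking field |
| --- | --- | --- | --- |
| Appendix B | Baseline only | Antibiotic among the options for treating diarrhoea | Places visited for diarrhoea, including pharmacy and drug seller |
| Appendix C | Two-weekly visit | None | Akala; other clinic |
| Appendix D | Per episode: "Use one form for follow-up of each diarrheal episode" | Daily row for other medicines, with a name field: "Name(s) of other meds taken for diarrhea" | Lwak; other clinic or hospital |
| Appendix E | Child seen at the clinic | Treatment list with several antibiotics | Not applicable |
| Appendix L | Village reporter visits | Zinc and ORS only | None |

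The rows of Appendix C are individually legible (symptoms, two care-seeking rows, signs on the day of visit), so the missing row does not look like a text-extraction loss. The planned linkages to demographic surveillance and stool culture data do not supply medicines either.

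Two results follow.

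- **Illness with diarrhoea.** Appendix D records other medicines and separates Lwak from other facilities, in both arms.
- **Illness without diarrhoea.** Only Appendix E records an antimicrobial, and only for children who attend Lwak.

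**What this does to a comparison.** The documents state no figure to reproduce, and every input here is an assumption. Let *a* be control-arm attendance at Lwak for illness without diarrhoea, *r* the home-to-control attendance ratio, *p* the probability of an antibiotic if the child attends and *q* the probability if not, with *p* and *q* equal in both arms.

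- Recorded risk ratio = (a·r·p)/(a·p) = r.
- True risk ratio = [a·r·p + (1 − a·r)·q] / [a·p + (1 − a)·q].

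For a = 0.5, r = 0.7, p = 0.4:

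- q = 0: 0.14/0.20 = 0.70, equal to the recorded 0.70, so no bias.
- q = 0.2: (0.14 + 0.65 × 0.2)/(0.20 + 0.50 × 0.2) = 0.27/0.30 = 0.90, against 0.70 recorded.
- q = 0.4: (0.14 + 0.65 × 0.4)/(0.20 + 0.50 × 0.4) = 0.40/0.40 = 1.00, against 0.70 recorded.

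Range with p = 0.4 and a from 0.3 to 0.5:

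| r (recorded ratio) | True ratio, q = 0 | True ratio, q = 0.2 | True ratio, q = 0.4 |
| --- | --- | --- | --- |
| 0.9 | 0.90 | 0.97–0.98 | 1.00 |
| 0.8 | 0.80 | 0.93–0.95 | 1.00 |
| 0.7 | 0.70 | 0.90–0.93 | 1.00 |

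With r = 1 the recorded and true ratios are both 1.00 for any q. Bias therefore needs both unequal attendance and antibiotics from elsewhere.

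Undercounting needs only the second condition. With a = 0.5, p = 0.4 and q = 0.2, the recorded risk is 0.20 and the true risk 0.30 in the control arm, so a third of use is missed.

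**The case against.** A reader might infer that fewer clinic visits in the home arm will make antimicrobial use look lower there. The documents do not support this as a prediction.

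- **The planned analysis is covered.** The antibiotic regression sits under treatment of diarrhoea. New episodes found at the two-weekly visit or in the clinic are followed up at 7 days with Appendix D, whose medicine field does not depend on clinic attendance.
- **No evidence of unequal attendance for illness without diarrhoea.** The Mali experience in the Background concerns zinc given alone for diarrhoea accompanied by other symptoms, and those episodes receive Appendix D. That control children must attend to obtain zinc also matters only for diarrhoea. Parents in the home arm are told that zinc is not adequate treatment for fever or cough. Referral rules and free Lwak care apply in both arms.
- **The size is assumed.** A recorded ratio of 0.70 is simply the attendance ratio put in.
- **The text already requires the record.** Data Management says forms will be field tested, and collection may move to handheld devices. The Akala label looks like a leftover, since Appendix F also mentions Akala clinic staff.

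The first three points stand and limit the finding to a gap in data capture. A further inference, that the planned clinic-visit outcome cannot separate Lwak from other facilities, fails too: that outcome concerns diarrhoea episodes, for which Appendix D has separate rows and Appendix E records each Lwak visit. The fourth point stands only in part. Field testing might catch the omission, but the form attached to the protocol contradicts the procedure, and objective 3 is wider than the analysis described.

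**Conclusion.** The contradiction between text and form is real and should be corrected. On the forms shown, follow-up records antimicrobials for illness without diarrhoea only at a Lwak visit, so that part of objective 3 cannot be answered from the household data. The missing medicine row is the main defect. The Akala label alone loses no antibiotic data, but it mixes Lwak visits with visits to all other facilities in the two-weekly record.

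The size of any bias is unknown. It is zero if attendance is equal or if no antibiotics come from outside Lwak, given equal prescribing probabilities in the two arms, and the documents give figures for neither condition. The primary outcome and the diarrhoea-episode analyses of antibiotic use and clinic visits are not affected. The conclusion assumes that the appended forms are the ones used in the field.

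**What to change.** - Add to Appendix C a medicine row giving the name of any antibiotic or antimalarial taken and its source (Lwak, other facility, pharmacy or drug seller, home).
- Replace the Akala row with a Lwak row, keeping the row for other clinics.
- State in Data Analysis that objective 3, for illness without diarrhoea, is taken from this two-weekly record in both arms.

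The cost is one form revision and brief field training. Caretakers' recall of drug names will be imperfect, but it is collected in the same way in both arms. The change must be in place before follow-up starts, because medicines not recorded at the visits cannot be reconstructed.

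### At household visits diarrhea is asked back to the last visit but zinc only for two weeks, so late visits undercount zinc days and a missed visit can hide some whole courses

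*Protocol*

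**What the plan says.** The Protocol, under Procedures for household visits, sets a two-week cycle: "Field workers will visit each enrolled child every 2weeks". At each visit it fixes two recall periods. For diarrhea: "S/he will ask about episodes of diarrhea since the last visit as well as current episodes". For zinc, the field worker asks about "any use of zinc in the last two weeks". It adds "The number of days of zinc and number of pills of zinc will be documented", with no period of its own, and "The interviewer will ask to see the zinc blister pack and record how many pills are remaining".

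Three later uses draw on these zinc data:

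- Secondary objective 5 covers zinc utilization in the two kinds of community, including "frequency of use and adherence to treatment instructions".
- Under Administration of zinc, a running check looks for zinc given without care being sought for fever or cough: "The use of zinc for episodes of diarrhea will be evaluated on a biweekly basis based on the data collected by the field workers".
- Under Calculation and comparison of prevalence rates, a Poisson regression in the zinc villages relates diarrhea prevalence to each child's total number of zinc days.

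Zinc is also recorded elsewhere. A newly identified episode gets a visit 7 days later (Follow-up of cases of diarrhea). Pills are counted on days 7 and 14 (Compliance monitoring). Appendix D has a day-by-day row for zinc taken. In home-zinc villages the village reporter asks about tablets used since the reporter's own last visit (Appendix L). Appendix C, the routine morbidity form, shows no zinc row, so the Protocol does not show how the two-week answer is written down.

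**The concern.** The diarrhea window stretches with the interval between visits and the zinc window does not. Once the interval exceeds 14 days, the first part of it is open to diarrhea reports but closed to zinc reports. Zinc days taken there drop out of the answer. If a whole course lies there, a treated episode meets a negative answer on zinc.

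What is at stake is the measurement of zinc use: how often it was used, how fully the course was taken, whether it was given alone, and each child's cumulative zinc days. The regression is exposed in a particular way, because diarrhea days from the uncovered stretch still enter the outcome while the zinc days from the same stretch can be missing from the explanatory variable.

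**Working it through.** The Protocol gives no figure for this point, so there is nothing to reproduce. The check is a count of how far the two windows overlap.

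**Inputs from the Protocol.** Planned interval 14 days and zinc window 14 days (Procedures for household visits). Course of 10 days, once daily (Administration of zinc). A 7-day course serves as a sensitivity value, because the Background reports an average of 7 days completed in the Bangladesh community trial.

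**Assumptions.** The actual interval is L days and the course starts on day s, with every s from 1 to L equally likely. Zinc is taken daily without gaps. The two weeks are applied literally, as days L − 13 to L. Only zinc taken by the day of the visit counts, and only courses begun within the interval.

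**Formulas.** Let e = L − 14 be the uncovered days and D the course length.

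- Zinc days taken by the visit: D(L − D + 1) + D(D − 1)/2.
- Zinc days lost: e(e + 1)/2 if e ≤ D, otherwise D(e − D) + D(D + 1)/2.
- Courses wholly unseen: those with s + D − 1 ≤ e, that is max(0, e − D + 1) of the L start days.

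**10-day course**

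| Interval L | Zinc days lost / taken | Share lost | Courses wholly unseen |
| --- | --- | --- | --- |
| 14 | 0 / 95 | 0% | 0 |
| 15 | 1 / 105 | 1% | 0 |
| 17 | 6 / 125 | 5% | 0 |
| 21 | 28 / 165 | 17% | 0 |
| 24 | 55 / 195 | 28% | 1/24 = 4% |
| 28 | 95 / 235 | 40% | 5/28 = 18% |

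At L = 28, for example, taken = 10 × 19 + 45 = 235 and lost = 10 × 4 + 55 = 95. A further 9 of the 28 start days (32%) give a course that is partly seen.

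**7-day course.** At L = 21: lost 28 of 126 = 22%, wholly unseen 1/21 = 5%. At L = 28: lost 77 of 175 = 44%, wholly unseen 8/28 = 29%.

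A full 10-day course is therefore wholly unseen only from L = 24, that is, a visit 10 or more days late. Up to 9 days late the two-week question still catches some of it.

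**After the change.** If the zinc question reaches back to the last visit, the uncovered stretch is empty at every L and the loss from mismatch is 0%.

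**How far the other records help.** These figures concern the two-week question alone.

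- The blister-pack count shows pills gone, but not when or for which episode. Home packs are reissued every 2 months whether or not the last was used, and Appendix L allows for tablets given to other family members.
- The day-7 visit, the later counts and Appendix D begin once an episode is identified at a routine visit or in the clinic. An episode treated at home without a clinic visit, and falling in a missed interval, is identified late or not at all by this route.
- Appendix L covers home-zinc villages only. Its visits are monthly for three months and then every three months.

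**The case against.** On the planned schedule the windows are identical, and the two-week phrase can be read as shorthand for the visit interval: the site description also asks about health seeking over the last two weeks at two-weekly visits. A loss needs both a late visit and a literal 14-day question. The Protocol gives no rate of late visits, and a fixed two-week recall has its own merit in limiting recall error for day and pill counts. Several other zinc records exist, and the primary comparison of diarrheal days by arm uses none of them.

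Much of this stands, and it keeps the point small. It does not remove it. The same paragraph words the two items differently, so a field worker following it after a gap would ask about different periods. The forms expect failed contacts: the enrollment form allows repeated attempts and an unavailable outcome, and Appendix L asks whether the caretaker was at home.

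A reader might infer that every late or missed visit turns treated episodes into untreated ones. The count does not support that: 10-day courses are cut short, not hidden, up to 9 days late, and after one missed visit 23 of 28 (82%) still reach the window. Nor do the documents support saying that the lost use cannot be recovered, since the pill counts and Appendices D and L recover part of it.

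**Conclusion.** The mismatch is real and minor. Taken alone, the two-week question loses about 17% of the zinc days of 10-day courses at a 21-day interval and about 40% at 28 days. At 28 days it misses about 18% of such courses entirely. These are averages over all start days under the assumptions above, before any credit for the other records. Restricting to courses begun in the first half of a 28-day gap gives 95/14 = 6.8 of 10 days lost, but that is the worst half and should not be read as typical.

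The trial-wide size cannot be computed without visit completion. A reader might also infer that the difference in zinc use between arms is understated. Home-treated episodes in a missed interval are the least protected, which makes this plausible. But Appendix L gives extra recovery in the home arm only, and visit completion by arm is not stated, so the net direction is not established.

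Secondary objective 5, the review of zinc given alone and the cumulative zinc-days regression are affected. The primary comparison is not.

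**What to change.** In Procedures for household visits, and on whichever routine form records the answer, ask about zinc use (days and pills) back to the last completed visit, the same period as for diarrhea. Appendix L already frames its zinc question this way. Record the date of the last completed visit on the form, so that a common fixed window can be applied to both items in a sensitivity analysis.

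The cost is one changed sentence, a form item and a date field, with no extra visits. The downside is somewhat longer recall of zinc days after a missed visit, which the sensitivity analysis can address. The change has to be made before data collection, because a period that was not asked about cannot be reliably filled in later.
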